### Enrollment and Randomization

After potential participants have signed the informed consent, their eligibility is evaluated based on the inclusion/exclusion criteria (Figure 1). If eligible, their demographic characteristics, medical history, and physical examination are assessed; both eyes are evaluated for visual acuity [Early Treatment Diabetic Retinopathy Study (ETDRS) chart test], retinal thickness (non-invasive optical coherence tomography, OCT), and retinal microvascular abnormalities (fundus biomicroscopy and/or fluoroangiography). Laboratory tests are also carried out to determine circulating levels of PRL, glycated hemoglobin, alanine aminotransferase, thyroid-stimulating hormone, and creatinine (Figure 1). The evaluations confirm eligibility, allow for the distribution of patients, and set the baseline reference for treatment comparisons. DME is diagnosed by means of ophthalmoscopy and OCT measurements of central retinal thickness (30). Patients are classified as having NPDR and PDR according to the international clinical DR severity scale (31). DME and NPDR patients are randomized in a 1:1 ratio to receive levosulpiride (25-mg orally TID for 4 weeks) or placebo (lactose pill orally TID for 4 weeks). PDR patients requiring vitrectomy (due to non-clearing vitreous hemorrhage, tractional retinal detachment, and/or severe neovascular proliferation) are randomly split 1:1 to receive levosulpiride (25-mg orally TID) or placebo (lactose pill orally TID) 1 week before undergoing vitrectomy. Patients requiring antiangiogenic therapy for the treatment of clinically significant DME are randomized to receive levosulpiride (25-mg orally TID) or placebo (lactose pill orally TID) during the 12 weeks of standard ranibizumab intravitreal therapy (0.5 mg every 4 weeks) (Figure 1). In all groups, the study medication is taken on top of standard therapy for diabetes, blood pressure control, or other medical conditions. Specifically, this therapy includes metformin, sulfonylureas, dipeptidyl peptidase-4 inhibitors, acarbose, insulin, ACE inhibitors or angiotensin II receptor blockers, beta blockers, calcium antagonists, and/or diuretics, etc. In the case of adverse and intolerable effects of the study medication, the treatment is stopped and reported as a failure (32).

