#### Exclusion Criteria

Not meeting inclusion criteria.History of ocular complications: severe myopia (>6 diopters), opacity of ocular media, glaucoma, ocular surgeries, and retinal detachment (except for PDR with vitrectomy)With retinal laser photocoagulation and/or intravitreal antiangiogenic therapy (<6 months before enrollment) (groups 1–4)With retinal laser photocoagulation and/or intravitreal antiangiogenic therapy (<6 weeks before enrollment) (groups 7 and 8)Prolactin serum levels >20 ng/mLLoss of kidney function (glomerular filtration rate <60 mL/min) for groups with DME, NPDR, and DME plus ranibizumabLoss of kidney function (glomerular filtration rate <30 mL/min) for groups with PDR undergoing vitrectomyContraindications for the use of levosulpiride (Parkinson’s disease, epilepsy, breast cancer, alcoholism, hypokalemia)Conditions inducing hyperprolactinemia including pathologies (hypothyrodism, hepatic dysfunction, prolactinomas) and medication (antipsychotics, antidepressants, prokinetics, estrogens, other)

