#### Secondary Outcome Measures

The secondary endpoints evaluate the safety of the study medication by measuring:
Blood pressureBlood glycated hemoglobinSerum glucoseSerum creatinineHyperprolactinemia-related side effects documented at each participant visit (32)Dopamine D2 receptor blocker side effects documented at each participant visit (32)

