### Safety Considerations

Levosulpiride is clinically approved and available in different countries (Italy, Spain, Germany, Belgium, Mexico, South Korea, etc). It is used at low doses (25–75 mg/day) as a prokinetic agent for the treatment of dysmotility-like functional dyspepsia (35, 36). It penetrates the blood–brain barrier poorly (37) so higher doses (800–2400 mg/day) are required for its use as an anti-depressant and anti-psychotic agent (38). Duration of treatment ranges from 1 week to more than 2 years (23). Low doses of levosulpiride are well tolerated during both acute and chronic administration. Heart rate and electrocardiogram are not altered (35) and sedation is rare (36). As the pituitary is outside the blood–brain barrier, low doses of levosulpiride increase serum PRL (39). Adverse effects of hyperprolactinemia include decreased libido, amenorrhea and infertility, breast engorgement and lactation, and gynecomastia (40). In a multicenter, double-blind, placebo-controlled trial of 408 dyspeptic patients receiving oral levosulpiride (25-mg TID for 4 weeks) the total incidence of hyperprolactinemia related disorders was 7% in female patients (41). More recently, a study in 342 dyspeptic female and male patients, using the same levosulpiride treatment, reported 40 patients (11%) with adverse effects (26.7% galactorrhea, 17.8% somnolence, 11% fatigue, and 11.5% headache), none of whom abandoned the study due to side effects (36).

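### Hypokalemia is an exclusion, but the listed enrollment tests include no potassium, so as listed only already-known cases can be excluded

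*Protocol article*

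**What the plan says.** The Exclusion Criteria section bars patients with contraindications to levosulpiride. After Parkinson's disease, the parenthesis that names them reads "epilepsy, breast cancer, alcoholism, hypokalemia". It gives no potassium threshold and no way of establishing the condition.

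The Enrollment and Randomization section describes what is done once consent is signed. On the clinical side, "their demographic characteristics, medical history, and physical examination are assessed", and both eyes are examined. On the laboratory side, "Laboratory tests are also carried out to determine circulating levels of PRL, glycated hemoglobin, alanine aminotransferase, thyroid-stimulating hormone, and creatinine". The section then gives the purpose of all this: "The evaluations confirm eligibility, allow for the distribution of patients, and set the baseline reference for treatment comparisons". It also lists the background drugs that patients may continue, among them "ACE inhibitors or angiotensin II receptor blockers, beta blockers, calcium antagonists, and/or diuretics".

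The Secondary Outcome Measures section opens with "The secondary endpoints evaluate the safety of the study medication by measuring". The blood tests that follow are glycated hemoglobin, glucose and creatinine.

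**The concern.** An exclusion protects patients only if it can be applied to those who meet it. Hypokalemia is defined by a blood value and may be unknown to the patient and the physician. The article names its enrollment blood tests one by one and gives the enrollment evaluations the task of confirming eligibility, yet the test that would establish this exclusion is not named.

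If a site ran the panel exactly as listed, a patient with unrecognised hypokalemia could be allocated to a drug that the protocol itself calls contraindicated. What is at stake is participant safety and the proper working of one eligibility criterion. The treatment comparison, the power and the type I error are not involved.

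**Working it through.** No calculation in the plan bears on this, so the check sets the sections side by side.

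**Step 1: match exclusions to tests.** The inputs are the Exclusion Criteria and the laboratory list under Enrollment and Randomization. I class five exclusions as depending on a laboratory value. The classification is mine, not the article's.

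| Exclusion | Test needed | In the enrollment list? |
|---|---|---|
| Serum prolactin above 20 ng/mL | PRL | yes |
| Reduced glomerular filtration rate (below 60 or below 30 mL/min, by group) | creatinine | yes |
| Hypothyroidism | TSH | yes |
| Hepatic dysfunction | ALT | yes |
| Hypokalemia | potassium | no |

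Four of five have a listed test. The fifth listed test, glycated hemoglobin, matches no exclusion but gives the baseline for a secondary outcome.

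**Step 2: look for potassium elsewhere.** It is 0 of the 5 enrollment tests and 0 of the 3 blood tests among the secondary outcomes. The visits described under Outcome Measures record history, examination, adverse events and those same outcomes. The only other serum measure among the outcomes is PRL. The text names no potassium or electrolyte measurement anywhere, so the listed follow-up tests would not pick up a case missed at enrollment.

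**Step 3: ask what else could detect it.** History and physical examination can reveal hypokalemia that has already been diagnosed, but they do not measure potassium.

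**Step 4: see whether pre-consent judgement is enough for laboratory criteria.** Under Current Status, 63 candidates signed consent and 9 were then excluded: 6 for low glomerular filtration rate, 1 for hyperprolactinemia, 1 for glaucoma and 1 requiring laser therapy. So 6 + 1 = 7 of the 9 exclusions rested on laboratory-type criteria, in people already identified as candidates. None was for hypokalemia. This does not show that a case was missed; it shows only that laboratory-type criteria do remove people after consent in this trial.

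**Step 5: exposure.** Of 120 planned patients, 120 / 2 = 60 would receive levosulpiride. A 1:1 ratio is stated for the DME, NPDR and PDR groups, and I assume an equal split for the ranibizumab groups. This is the number allocated to the drug. The number with unrecognised hypokalemia cannot be derived, because the article gives no prevalence and no share or type of diuretic.

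**The case against.** The best reply is that this is a condensed article and its laboratory list need not be complete. There is direct evidence for that: serum glucose is a secondary outcome, and the enrollment evaluations are said to set the baseline, yet glucose is missing from the list too. Figure 1 is cited for both eligibility and the laboratory tests, and it is not shown. Its caption expands abbreviations such as HbA1c, ALT and TSH and mentions no electrolyte, but potassium need not be abbreviated, so that says little. This part of the reply stands: the text does not establish that potassium goes unmeasured. The difference from glucose is that glucose is not an exclusion criterion, so its absence leaves no exclusion unchecked.

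A second reply is that the sentence about confirming eligibility covers history and examination as well as the blood tests, and that the other contraindications grouped with hypokalemia have no dedicated test either. That is correct, and applying the whole group from history and records is a coherent procedure. It is weaker for hypokalemia than for Parkinson's disease, epilepsy, breast cancer or alcoholism, which history can ordinarily bring out.

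Three stronger readings are tempting, and the document supports none of them:

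- A reader might infer that permitted diuretics make undetected hypokalemia likely. The article does not say which diuretics are taken, by how many patients, or that they lower potassium. The link is an assumption about drug class, and the point does not need it.
- A reader might infer a cardiac danger. The Safety Considerations section says of low doses, "Heart rate and electrocardiogram are not altered". That statement is not specific to hypokalemic patients, but nothing in the article shows a particular harm in them.
- A reader might take the 60 patients on levosulpiride as the number at risk. It is only the number allocated to the drug.

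**Conclusion.** The point holds as a minor, low-cost safety improvement. The protocol names hypokalemia as a contraindication, and the tests it lists cannot identify an unrecognised case, while the prolactin, kidney, thyroid and liver exclusions each have a test. As listed, the exclusion reaches only patients whose hypokalemia is already known.

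The conclusion assumes that the five named tests are the ones run, which the article does not say outright. If the full protocol or Figure 1 includes potassium, what remains is a gap in the article's list, not in patient protection. The size of the risk cannot be estimated. Nothing here affects an efficacy estimate, the sample size or an error rate.

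**What to change.** Add serum potassium to the enrollment panel, run on the blood already drawn for creatinine. State in the Exclusion Criteria that a value below the laboratory's lower reference limit counts as hypokalemia, and require the result before randomisation. If potassium is already measured, name it in the enrollment list and give the cut-off.

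The cost is one routine analyte, with no extra visit or procedure. A few candidates may be excluded or wait briefly for the result, though the prolactin and creatinine results have to be back before allocation in any case.

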**Methods:**

It is a prospective, randomized, double-blind, placebo-controlled trial enrolling male and female patients with type 2 diabetes having DME, non-proliferative DR (NPDR), proliferative DR (PDR) requiring vitrectomy, and DME plus standard intravitreal therapy with the antiangiogenic agent, ranibizumab. Patients are randomized to receive placebo (lactose pill, orally TID) or levosulpiride (75 mg/day orally TID) for 8 weeks (DME and NPDR), 1 week (the period before vitrectomy in PDR), or 12 weeks (DME plus ranibizumab). In all cases the study medication is taken on top of standard therapy for diabetes, blood pressure control, or other medical conditions. Primary endpoints in groups 1 and 2 (DME: placebo and levosulpiride), groups 3 and 4 (NPDR: placebo and levosulpiride), and groups 7 and 8 (DME plus ranibizumab: placebo and levosulpiride) are changes from baseline in visual acuity, retinal thickness assessed by optical coherence tomography, and retinal microvascular abnormalities evaluated by fundus biomicroscopy and fluorescein angiography. Changes in serum PRL levels and of PRL and vasoinhibins levels in the vitreous between groups 5 and 6 (PDR undergoing vitrectomy: placebo and levosulpiride) serve as proof of principle that PRL enters the eye to counteract disease progression. Secondary endpoints are changes during the follow-up of health and metabolic parameters (blood pressure, glycated hemoglobin, and serum levels of glucose and creatinine). A total of 120 patients are being recruited.

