### Outcome Measures

After enrollment, four study visits take place every 2 weeks during a follow-up period of 8 weeks in groups 1 and 2 (DME: placebo and levosulpiride) and groups 3 and 4 (NPDR: placebo and levosulpiride). For groups 7 and 8 (DME plus ranibizumab: placebo and levosulpiride) enrollment is followed by three visits, one every 4 weeks (at the time of ranibizumab intravitreal delivery). At each visit, the medical history, physical examination, adverse events, and primary and secondary outcomes are documented. For groups 5 and 6 (PDR requiring vitrectomy: placebo and levosulpiride), there is only one visit 1 week after enrollment, i.e., at the time of vitrectomy.

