### Sample Size

The proposed sample size (Figure 1) was calculated according to expected differences in visual acuity, the main parameter of visual function. Using the formula for mean differences and the reported changes in visual acuity (33, 34), we considered a difference of 10 letters in the ETDRS chart test between baseline and after intervention, a SD of 10, a power 1 − β = 80%, and a type-I error rate of 5%. For PRL and vasoinhibin level outcome, sample size is in accord to experimental models of DR and clinical experience (14, 15). As the study progresses, the study may need to accommodate a different sample size to obtain clinically relevant and statistically significant differences, access to eligible patients, elimination of patients, etc.

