### Strengths and Limitations of the Study

A strength of the study is the use of an oral therapy with a medication regimen that has been proven safe in diabetic patients (36). Adverse side effects (galactorrhea, somnolence, fatigue, and headache) are mild and rare, decline with time, and usually do not result in patients abandoning the study (36). In our protocol, side effects and risks are further minimized by frequent medical supervision (every 2 weeks) and short treatment duration (2 months) when administered as monotherapy. Its use as a combination therapy with ranibizumab, not only reduces ophthalmological risks, as patients are being treated with the standard therapy, but extends possible beneficial effects to patients with clinically significant DME, the major diabetic population requesting eye-care in underdeveloped countries. The absence of levosulpiride clinical studies in diabetic patients with retinal and renal microvascular complications limits the study design. We are aware that the follow-up period may be too short to provide specific treatment recommendations, but the short-term results could encourage further prospective studies with different treatment regimen and longer follow-up. Levosulpiride retains its potency to induce hyperprolactinemia at very low doses (38), so smaller doses coupled to long-term treatments can be a desirable therapy.

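### Study medication in the DME and NPDR groups is stated as 4 weeks in one section and 8 weeks or 2 months in two others, leaving it unclear whether the week-6 and week-8 outcomes are on or off drug

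*Protocol article*

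**What the plan says.** Three places in the protocol article state how long groups 1 to 4 take study medication.

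- Enrollment and Randomization, the section that assigns treatment: "levosulpiride (25-mg orally TID for 4 weeks) or placebo (lactose pill orally TID for 4 weeks". The 4 weeks is written separately for each arm.
- Abstract, Methods: study medication is given "for 8 weeks (DME and NPDR), 1 week (the period before vitrectomy in PDR), or 12 weeks (DME plus ranibizumab".
- Strengths and Limitations of the Study: risks are said to be reduced by a "short treatment duration (2 months) when administered as monotherapy".

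The Outcome Measures section sets the assessment schedule for these groups: "four study visits take place every 2 weeks during a follow-up period of 8 weeks". It adds: "At each visit, the medical history, physical examination, adverse events, and primary and secondary outcomes are documented". That section describes follow-up and does not say how long medication continues.

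**The concern.** A reader who follows the treatment-assignment section gives medication for half as long as a reader who follows the Abstract. Three things depend on which is meant.

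The first is what the main comparisons in groups 1 to 4 estimate. The Objectives section frames the trial around prolonged exposure to prolactin (PRL), so the length of exposure is part of the question. A final-visit difference in visual acuity or retinal thickness means one thing at the end of dosing and another 4 weeks later.

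The second is who remains in the analysis. The Elimination Criteria remove patients who do not comply with study medication, as judged by returned tablets and circulating PRL. Neither can be judged without knowing how many doses were due and over what period.

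The third is the safety exposure period. The article itself uses the short duration as an argument that risk is limited.

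**Working it through.** **Inputs.** Duration of 4 weeks (Enrollment and Randomization); 8 weeks (Abstract); 2 months, taken as about 8 weeks (Strengths and Limitations). Visits: four, every 2 weeks (Outcome Measures). Dosing three times a day. Total enrolment 120, in eight arms.

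**The plan's own figure.** 4 visits × 2 weeks = 8 weeks of follow-up, which matches the text. Visits fall at weeks 2, 4, 6 and 8.

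**Does the 2-month statement apply to groups 1 to 4?** Yes. The same sentence refers to supervision every 2 weeks and to use as monotherapy. Among the four populations, only DME and NPDR have 2-weekly visits. The vitrectomy groups have one visit at 1 week, and the ranibizumab groups are seen every 4 weeks.

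**Visits on and off drug (a visit is off drug if its week is later than the end of dosing).**

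| Stated duration | On drug | Off drug | Share off drug |
|---|---|---|---|
| 4 weeks | weeks 2, 4 | weeks 6, 8 | 2/4 = 50% |
| 8 weeks | weeks 2, 4, 6, 8 | none | 0/4 = 0% |

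At the final visit, time since the end of dosing is 8 − 4 = 4 weeks under the first reading and 8 − 8 = 0 weeks under the second.

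**Exposure and compliance count.** Doses due are 3 × 7 × weeks: 3 × 7 × 4 = 84, or 3 × 7 × 8 = 168. The ratio is 168/84 = 2. A patient who followed the 4-week text exactly would have taken 84/168 = 50% of the doses due under the 8-week text.

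**Patients concerned.** Group sizes are not in the visible text. If the arms are equal, 120/8 = 15 per arm and 4 × 15 = 60 patients.

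**Is the conflict confined to these groups?** Yes. The Abstract and the Enrollment and Randomization section agree on 1 week before vitrectomy and on 12 weeks with ranibizumab.

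**Sample size.** The stated inputs (a 10-letter difference, SD 10, 80% power, 5% type-I error) contain no duration, so that arithmetic is unaffected.

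**The case against.** The strongest reply is that this is a slip in a condensed article. The full protocol or Figure 1, neither of which is shown, may state one clear duration, and a single centre with 45 completers by January 2018 must have been working to some schedule. This is a fair limit on what can be inferred. It does not remove the conflict, because the article's text disagrees with itself whatever the figure says, and one of the disagreeing statements is the treatment assignment itself. The only amendment described under Current Status added the ranibizumab groups and does not explain the difference.

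Three stronger readings are tempting, and the document does not support them.

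- A reader might infer that the 8-week visit schedule is a further contradiction. It is not: follow-up after the end of dosing is a legitimate design, so the schedule fits either duration. It only shows the consequence.
- A reader might infer that patients received different durations and that the estimate is uninterpretable. Nothing in the article says so. Even if durations had differed, both arms of each pair are assigned the same duration in every statement, so the randomised comparison would average over durations. That is harder to interpret but not meaningless.
- A reader might infer that adjusting for duration would repair the matter. Duration actually taken is determined after randomisation, and adjusting for it could bias the treatment comparison.

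Current Status reports three losses after randomisation for non-compliance. Their groups are not given, so they cannot be attributed to this conflict.

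**Conclusion.** Wrong as written. The article gives two incompatible durations of study medication, differing by a factor of two, for four of its eight arms. These arms make up both comparisons of levosulpiride with placebo as monotherapy for DME and NPDR. The duration decides whether 2 of 4 outcome visits, including the last, are on or off treatment, and whether 84 or 168 doses are due.

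The contradiction rests on the text alone and needs no assumption. Two of the size figures do rest on assumptions: visits held on schedule at weeks 2, 4, 6 and 8, and equal arms for the figure of about 60 patients. What patients actually received is unknown from this document, and no claim is made about it.

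**What to change.** Reconcile the Abstract, the Enrollment and Randomization section and the Strengths and Limitations section to one stated duration for groups 1 to 4. The sponsor must say which it is; this review does not choose. In the Outcome Measures section, state whether the week-6 and week-8 visits are on or off treatment, and have the tablet count used under the Elimination Criteria follow from the same duration.

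Confirm from dispensing and tablet-return records what patients already enrolled were given. If the records show that more than one duration was planned for different patients, report results by planned duration within the randomised comparison, and do not adjust for the duration actually taken.

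The cost is small: a correction to the article, a clarifying amendment if the full protocol carries the same conflict, and a records check at one centre. As of January 2018, 54 patients remained after exclusions, out of 120 planned, so the clarification would still reach much of the enrolment planned at that date.
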